## Abstract

**Background:**

Early infant diagnosis among human immunodeficiency virus (HIV)-exposed infants is a critical component of prevention of mother-to-child transmission programs. Barriers to early infant diagnosis include poor uptake, low retention at designated re-testing intervals, delayed test results, passive systems of communication, and poor linkage to treatment. This study will evaluate the HIV Infant Tracking System (HITSystem), an eHealth intervention that streamlines communication and accountability between the key early infant diagnosis stakeholders: HIV+ mothers and their HIV-exposed infants, healthcare providers, and central laboratory personnel. It is hypothesized that the HITSystem will significantly improve early infant diagnosis retention at 9 and 18 months postnatal and the timely provision of services.

**Methods/design:**

Using a phased cluster-randomized controlled trial design, we will evaluate the impact of the HITSystem on eight primary benchmarks in the 18-month long cascade of care for early infant diagnosis. Study sites are six government hospitals in Kenya matched on geographic region, resource level, and patient volume. Early infant diagnosis outcomes of mother-infant dyads (*n* = 120 per site) at intervention hospitals (*n* = 3) where the HITSystem is deployed at baseline will be compared to the matched control sites providing standard care. After allowing for sufficient time for enrollment and 18-month follow-up of dyads, the HITSystem will be deployed at the control sites in the end of Year 3. Primary outcomes are retention among mother-infant dyads, initiation of antiretroviral therapy among HIV-infected infants, and the proportion of services delivered within the optimal time window indicated by national and study guidelines. Satisfaction interviews with participants and providers will inform intervention improvements. Cost-effectiveness analyses will be conducted to inform the sustainability of the HITSystem. Hypothesized outcomes include significantly higher retention throughout the 18-month early infant diagnosis process, significantly more services provided on-time at intervention sites, and a potential savings to the healthcare system.

**Discussion:**

This study will evaluate the public health impact of the HITSystem to improve critical early infant diagnosis outcomes in low-resource settings. Cost-effectiveness analyses will inform the feasibility of scale-up in other settings.

**Trial registration:**

ClinicalTrials.gov: NCT02072603

## Background

While early infant diagnosis (EID) and prompt treatment of human immunodeficiency virus (HIV)+ infants are critical components of prevention of mother-to-child transmission (PMTCT) efforts, EID has received minimal attention compared to other HIV prevention and treatment services. The primary objective of EID is to promptly identify HIV-infected infants to initiate live-saving antiretroviral therapy (ART) as soon as possible [1, 2]. Beyond facilitating prompt ART initiation, EID provides critical reassurance to families whose infants are uninfected and allows implementation of feeding plans designed to minimize risk of transmission or optimize survival among those identified as HIV-infected [3]. Similarly, EID and infant feeding methods inform postnatal ART prophylaxis recommendations [4].

EID care and management includes an algorithm and series of interventions known as the “EID cascade of care”. This cascade includes the following: (1) the offer and acceptance of EID testing among HIV-exposed infants, (2) accurate specimen collection, transport, and laboratory processing; (3) relay of results to both healthcare providers and mothers/caregivers; and (4) linkage to care: OI prophylaxis for all HIV-exposed infants (cotrimoxazole for *pneumocystis jiroveci* pneumonia) and ART for HIV+ infants [5]. Because HIV infection cannot be definitively excluded until at least 6 weeks after cessation of breastfeeding, re-testing infants who initially test negative is critical to identify instances of postnatal HIV transmission. Kenyan EID guidelines call for routine re-testing of HIV-exposed infants at 9 and 18 months postnatal [6].

Although the guidelines provide clear objectives, challenges at every step in the EID cascade of care compromise the quality of EID services provided in Kenya and other low-resource settings [5, 7–9]. Infant testing often occurs after the recommended 6 weeks of age (average age of 3.1 months) [8, 10, 11], and turn-around times for results are typically quite long (average of 1–3 months) [10]. Retention throughout the recommended 18-month postnatal period is low (32–74.7 %) [8, 12] and less than one-third of Kenya’s HIV-infected infants are initiated on ART [6, 13]. Transportation, documentation, and communication challenges contribute to lost or delayed samples [5, 7], and a passive system for mother notification or follow-up leads to delayed care and missed opportunities to support retention [14–16]. Limited coordination between EID stakeholders limits accountability, efficiency, and linkage to treatment [5, 17]. In addition to these system-level challenges, mothers experience individual barriers that limit their full participation in the EID process (e.g., lack of: awareness of the existence or importance of EID services, resources for transportation, and fear of disclosure of their HIV status) [18, 19].

Our study aims to evaluate the HIV Infant Tracking System (HITSystem), a web-based tool designed to address many of the barriers in current EID service provision in Kenya, with the ultimate goal of maximizing the quality of EID services. As a system-level intervention, it was not deemed feasible or acceptable to randomize at the individual level; therefore, randomization occurred at the site (hospital) level. Primary outcomes will be measured at the participant (mother-infant dyad) level and aggregated to report outcomes per hospital. The primary outcomes for efficacy of the HITSystem are retention through the EID Cascade of Care (measured by eight unique benchmarks between 0–18 months postnatal, including ART initiation among HIV-infected infants) (Table 1) and efficiency of services (turn-around times for EID services and ability to meet age and time-specific targets with the HITSystem compared to control sites where standard of care services are provided). Secondary outcomes are maternal and infant predictors of retention, postnatal period(s) at the highest risk for loss to follow-up, satisfaction among mothers and providers, and infant HIV infection status over time. Cost-effectiveness analyses will quantify resources required to implement the HITSystem versus standard EID services and calculate potential short and long-term costs averted by this intervention to inform scale-up and sustainability.

**Table 1 Tab1:** HITSystem targets: eight time-sensitive EID interventions

1.Initiation of OI prophylaxis at 6 weeks
2.Collect dried blood spot (DBS) for PCR test by 6 weeks
3.Receipt of DBS at lab within 10 days of collection
4.Return of PCR results from lab within 2 weeks
5.Notify mother within 2 weeks of the EID provider receiving results
6.Initiate all HIV-infected infants on ART within 4 weeks of notifying the mother
7.Retest all HIV-uninfected infants at 9 months, initiate ART w/in 4 weeks if applicable^a^
8.Retest all HIV-uninfected infants at 18 months, initiate ART w/in 4 weeks if applicable^a^

^a^Re-testing indicated at these time points or 6 weeks after cessation of breastfeeding

Greater detail regarding the 8 intervention points and the HITSystem process has been previously published. [21]

## Methods/design

### Trial design

This is a 5-year phased cluster-randomized, controlled trial design to rigorously evaluate the impact of the HITSystem in Kenya. Study sites are six government hospitals in Kenya matched on geographic region, resource level, and patient volume to produce three-matched pairs. One hospital in each pair was randomly assigned to either the intervention (HITSystem) or control group (standard of care) condition; resulting in three interventions and three control study sites. We anticipate a 12-month window to complete enrollment of *n* = 120 mother-infant dyads per hospital, followed by an 18-month follow-up period (until end of Year 3). In Year 4 the HITSystem will cross over to initial control sites whose standard of care data from the 12 months prior will serve as a comparison for analyses.

### Recruitment, participants, and setting

This study is being conducted at government hospitals at the provincial, county, and sub-county levels in Kenya. The study protocol is in compliance with the Helsinki Declaration and was reviewed and approved by the Institutional Review Boards at the Kenya Medical Research Institute (protocol #2726) and the University of Kansas Medical Center (protocol #13793). Matched hospitals meet the following selection criteria: government funded; provide PMTCT, EID, and ART services; have at least one dedicated EID provider; and maintain medical files for HIV-exposed infants. Matched hospitals reflect regional differences in HIV prevalence, geography (e.g., average travel distance to clinic, accessible transportation), and cultural influences (e.g., tribal practices, religious beliefs).

### Participant eligibility and consent

As a system-level intervention, any HIV-infected mother whose infant is <18 months at the time of initial enrollment in EID and presents for care through the Maternal and Child Health (MCH) department is eligible to be enrolled in the HITSystem. Mothers <18 years of age or who present for care through other departments can utilize the HITSystem, but their data will be exempted from analyses. Cell phone ownership is not a requirement for participation. Mothers are informed about the HITSystem during enrollment by trained research or clinical staff, and those wanting to participate provide written informed consent prior to enrollment or completion of the baseline survey. A separate informed consent is conducted prior to the satisfaction interview near the time of 9-month re-testing. Those who wish to opt out receive the paper-based standard of care. Based on our pilot experience, we anticipate >95 % participation.

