### Participant enrollment

When a mother first presents her infant for EID, the EID provider creates a new infant record in the EID Registry notebook (SOC) or the HITSystem (intervention), and data regarding her antenatal care, maternal ARV prophylaxis regimens, and postpartum infant prophylaxis are entered. The mother’s cell phone number is also recorded in the HITSystem at this time. The majority of mothers have cell phones (97 % in urban and 82 % in peri-urban pilot hospitals) ([name] et al., Lessons learned from implementing the HIV Infant Tracking System (HITSystem) to improve early infant diagnosis of HIV outcomes in Kenya, submitted) [22], but for the few mothers without access or who prefer not to use their cell phones, we ask for a hand drawn map from the clinic to their home or major landmark to assist follow-up efforts. At subsequent consultations (PCR test results, 9 month re-testing, etc.), the infant’s information is updated in the EID Registry notebook (SOC) or pulled up electronically on the HITSystem and populated with additional data (intervention).

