##### EID retention

EID retention will be characterized as complete or incomplete. Incomplete EID care (loss to follow-up) is defined as one or more of the following: (1) DBS not collected, (2) mother not notified of result, (3) HIV-infected infant not started on ART, (4) HIV-uninfected infant not re-tested at 9 months, and 5) HIV-uninfected infant not re-tested at 18 months.

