To assess the impact of the HITSystem on timely administration of eight critical EID interventions (Optimal EID Care Index), we will analyze data using multilevel modeling (Proc MIXED in the SAS System version 9.4) [24] to account for the nesting of time within dyad within hospital. This will increase the precision of treatment effect estimates by more correctly estimating standard errors (that are not correctly estimated when nesting is ignored) and indicate inferences about change over time by condition. We will include covariates that may be associated with EID completion (e.g., infant sex, distance from hospital, cell phone ownership) in addition to any pre-intervention differences identified across conditions and hospitals. Outcome variables of interest include an aggregate score and sub-scale scores (based on the Optimal EID Care Index), infant age at first PCR test, proportion re-tested by 9 months, and proportion re-tested by 18 months.

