## Discussion

While previous efforts have been made to improve EID through the utilization of various interventions targeting only one of the key players in the EID system (most often the hospital or laboratory) [11, 16, 27–30], the HITSystem is the first system to comprehensively link multiple stakeholders (health facilities, mother-infant pairs, and laboratories) with an interactive tool that facilitates multidirectional communication, data management, and outcomes monitoring.

The web-based nature of the system minimizes the impact of geographical challenges to the current system, and this intervention relies heavily on the current communications infrastructures, reducing the need for costly hardware and system upgrades. This study will allow an analysis of outcomes at each step of the EID cascade of care and will facilitate identification of specific challenges within the participating facilities. Previous studies related to system-level interventions addressing EID have been limited to observational or quasi-experimental studies in which historical data served as the basis for comparison. The rigor of this study, as a RCT, greatly increases the value of the comparative data and will facilitate identification of improvements related to the intervention versus those resulting from the maturation of EID practices over time.

The intervention is applicable to all HIV-exposed infants and their mothers/guardians, given its adaptability regardless of cell phone ownership or literacy. However, it is only able to address outcomes in those mothers who present themselves for care at facilities. The intervention targets quality of care for clinic-based populations, and the study makes no attempt to directly target EID uptake. Although the study focuses on a system-level intervention, the HITSystem’s ability to capture and analyze individual factors that may influence EID retention will form the basis for exploration in further studies. Given the rapid pace of technological innovation in Kenya, the clean study design may be challenged by the introduction of other eHealth interventions at study sites that may influence existing processes for care. Every effort will be made to control for external influences in the design and analyses.

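### Infants may enrol at any age under 18 months, yet several age-based outcomes make no exception for targets that passed before enrolment

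*Protocol article*

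**What the plan says.** **Entry.** Under Participant eligibility and consent, a mother qualifies if she is one "whose infant is <18 months at the time of initial enrollment in EID". Under Participant enrollment, tracking begins at first contact: "When a mother first presents her infant for EID, the EID provider creates a new infant record". The Discussion adds that "the study makes no attempt to directly target EID uptake".

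**Age-based targets.** Table 1 includes "Initiation of OI prophylaxis at 6 weeks" (item 1) and "Collect dried blood spot (DBS) for PCR test by 6 weeks" (item 2), with re-tests at 9 and 18 months (items 7 and 8). Its footnote allows a re-test at those ages or 6 weeks after breastfeeding stops.

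**Scoring.** Under Timely delivery of EID Services, each of the eight items scores 0 (never done), 1 (done late) or 2 (done on time), summed to 0–16 for every dyad. Under EID retention, one of the five ways to be incomplete is "HIV-uninfected infant not re-tested at 9 months".

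**Impact outcomes.** Statistical analyses lists, besides the index, "infant age at first PCR test, proportion re-tested by 9 months, and proportion re-tested by 18 months". The covariates given as examples are infant sex, distance from hospital and cell phone ownership. Other variables enter if they differ significantly before the intervention.

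**The concern.** The intervention starts when the infant's record is created, but some outcomes are clocked from birth. For an infant who first presents after a target age, the hospital can no longer meet that target, whichever arm it is in. Followed as written, the rules then count lateness before enrolment as a failure of the service being tested.

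Age at first PCR is the clearest case. It is age at enrolment plus delay after enrolment, and for a late presenter the HITSystem can shorten only the second part.

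Two things are at stake. Outcomes that neither arm can change dilute a true effect. And with only six hospitals, matched on region, resource level and volume, age at presentation may differ between arms by chance. Such a difference would appear as an effect on timeliness.

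**Working it through.** The article states no figure on this point, so there is none to reproduce. The check sets the entry rule against each outcome and then shows how the consequence scales.

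**1. Which outcomes are affected**

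- Items 1 and 2, on-time point: unattainable for an infant enrolled after 6 weeks who had no earlier services. Late completion still scores 1.
- Item 7, on-time point: unattainable for an infant enrolled well after 9 months, if judged by age alone. The breastfeeding footnote may give another valid time.
- Proportion re-tested by 9 months: unattainable for an infant enrolled after 9 months.
- Age at first PCR: cannot be lower than age at enrolment, unless a test was done earlier.
- Retention, 9-month criterion: possibly affected. The definition has no age window and does not mention the footnote.
- Retention, DBS criterion: not affected, since DBS collected at any age counts.
- Items 3 to 6: not affected, since they run from collection, receipt of results or notification. Item 8 still lies ahead for every eligible infant.

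**2. Index ceiling, taking the article's maximum of 16**

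- Enrolled after 6 weeks, no earlier services: 16 − 1 − 1 = 14.
- Enrolled well after 9 months, item 7 done but counted late: 14 − 1 = 13.
- The same, item 7 never done: 14 − 2 = 12.

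**3. Dilution of on-time DBS**

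Let q be the share enrolled after 6 weeks with no earlier DBS. The on-time proportion cannot exceed 1 − q, and an effect d among early presenters becomes d × (1 − q). The values of q and d = 20 points are assumptions.

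| q | Ceiling | 20-point effect becomes |
|---|---|---|
| 0.2 | 80% | 16 points |
| 0.4 | 60% | 12 points |
| 0.6 | 40% | 8 points |
| 0.8 | 20% | 4 points |

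**4. Chance imbalance**

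Assume no intervention effect and 80% on time among early presenters in both arms. The spurious difference in on-time DBS is 0.80 × (difference in q).

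- q of 0.4 and 0.5: 0.80 × 0.10 = 8 points.
- q of 0.4 and 0.6: 0.80 × 0.20 = 16 points.

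Over items 1 and 2 together, that is 2 × 0.08 = 0.16 and 2 × 0.16 = 0.32 index points.

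**5. Age at first PCR**

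The Background reports that "Infant testing often occurs after the recommended 6 weeks of age (average age of 3.1 months"). That mean is 3.1 × 30.44 / 7 = 13.5 weeks. With an assumed mean delay after enrolment of 0 to 4 weeks, the part already fixed at enrolment is between (13.5 − 4) / 13.5 = 70% and 100%.

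**The case against.** The strongest reply is that the conflict is narrower than it looks and already partly guarded against.

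- **Retention.** A reader might infer that every infant enrolled after 9 months is incomplete whatever the hospital does, or that missing the 6-week targets counts as loss to follow-up. The documents support neither. The footnote gives some late entrants a valid re-test time, the retention criterion has no age window, and it applies only to uninfected infants. OI prophylaxis is not a retention criterion. This part of the reply stands in full.
- **Size.** A reader might take the 3.1-month mean to show that the typical study infant has already lost two points. It is a literature mean of age at testing, not age at enrolment at these hospitals, and a mean need not describe the typical infant. For infants enrolled before 6 weeks, alerts set from date of birth can still change DBS timing. This also stands.
- **Safeguards.** Hospitals were matched, Table 1 outcomes were reviewed for the 12 months before the study, and the covariate list is open. These help, but the matching was not on age at presentation. A significance screen is weak protection, because with six hospitals an imbalance large enough to matter need not be significant.
- **Detail for an analysis plan.** Denominators and covariate lists are commonly left to it. But the article itself fixes the scoring rules and names these impact outcomes, and those rules produce the problem.
- **Estimand.** Scoring every presenting infant is a defensible pragmatic choice, and age at enrolment is observed after hospitals were randomised. This is why the all-infant result should be kept alongside.

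**Conclusion.** The point holds for the on-time points of items 1, 2 and 7, the proportion re-tested by 9 months and age at first PCR, and possibly for the 9-month criterion of retention. The certain part is structural: a ceiling of 14 of 16 for an infant enrolled after 6 weeks without earlier services, and an unattainable 9-month outcome for one enrolled after 9 months.

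Because eligibility is the same in both arms, the expected consequence is dilution. Bias needs a chance difference in age at enrolment between the arms, which is possible with three hospitals in each but not shown. The article gives no distribution of age at enrolment, so the dilution and imbalance figures are illustrations under assumed shares, not estimates for this trial. That age at first PCR is largely fixed at enrolment is an inference from the literature mean and an assumed delay. The matter is worth correcting before analysis, and the article reports that no analyses have yet been done.

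**What to change.** In the analysis plan:

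1. Pre-specify age at enrolment, from date of birth and enrolment date, as a covariate in the retention, index and timing models, whether or not it differs significantly between arms.
2. Score the on-time points of items 1 and 2 among infants enrolled by 6 weeks, and the 9-month re-test among HIV-uninfected infants enrolled before 9 months. Give the all-infant result as a sensitivity analysis.
3. Use delayed entry in the survival analysis, so that each infant is at risk only from enrolment.
4. Report age at first PCR descriptively. For the intervention effect, use DBS delay counted from the later of enrolment and 6 weeks of age. Counting simply from enrolment would penalise good timing: an infant enrolled at 1 week and tested at 6 weeks would score (6 − 1) × 7 = 35 days, and one enrolled at 12 weeks and tested the next day would score 1.

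The cost is a smaller denominator for the early benchmarks and selection on age at presentation. The plan says the intervention does not target uptake, so that selection should be largely unrelated to arm, and the all-infant result provides a check. Eligibility and care are unchanged.

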### Standard of care

The current standard of care (SOC) for EID in Kenya has many well-documented challenges [8, 10, 11, 17]; however, when effectively implemented as designed, the following should take place: The EID provider should gather information on relevant maternal and infant clinical and demographic data at the time of postnatal enrollment in EID. These data should be entered in a large paper registry book (HIV-Exposed Infant Registry), organized by month of birth. Dried blood spot samples should be collected at the targeted age of 6 weeks and sent via courier to the central laboratory for processing. The samples should then be processed at the lab and paper polymerase chain reaction (PCR) test results returned to the hospital via courier and then sent to MCH to be added to the mother-infant file and recorded in the EID registry. If the infant has an HIV-positive test result, EID staff should contact the mother via phone to ask her to return to the clinic where she should be counseled about the HIV-positive result and referred to the Comprehensive Care Center (CCC) where a first line pediatric ART regimen should be initiated [6, 20]. If the result of the initial PCR test is negative, the result should be noted in the paper registry and the mother should be informed at a subsequent clinic visit and advised to return with the infant for a re-test at 9 months of age. At 9-months postnatal, all HIV-exposed infants should receive an antibody test, and if positive, a confirmatory PCR test should be conducted using the previously described process for PCR testing. If the antibody result is negative, the mother should be asked to return 6 weeks after the cessation of breastfeeding or when the infant is 18 months old to repeat this process. Even when implemented as designed, the current SOC for EID has multiple gaps where mothers often fall out of care, employ extremely limited prospective tracking to identify when services are indicated, and rely on a passive system for communicating test results to mothers. These shortcomings combined with well-documented challenges involving delayed or lost samples resulting in long turn-around time for infant test results combine to produce the observed poor retention and completion rates [8, 10, 11, 17].

